### Sample size calculation

Sample size was determined based on a study
[15] where the average defecation rate of patients with functional constipation was 2.6 times per week with a standard deviation of 2.2 after drug treatment, and a 1.4-fold difference in the clinical effects between the drug and the placebo is considered to be of clinical relevance. In this study, we anticipated that an improvement of the mean defecating frequency is 4.0 after acupuncture treatment, with a standard deviation of 3. To detect this difference, we need a sample size of 71 in each group (α = 0.05, β = 0.10)
[16]. To allow 15% for loss to follow up, our proposed trial requires 243 patients (81 for each group).

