## Methods and Design

### Design

This is a multicenter randomized controlled, three-arm trial enrolling both men and women with functional constipation in China. This study will be conducted at Tongji Hospital affiliated to Tongji Medical College, Huazhong University of Science and Technology; Hubei Provincial Hospital of TCM; Hospital of Huazhong University of Science and Technology. Tongji Hospital is the central structure of the study. The participants will be allocated through complete randomization in a 1:1:1 ratio. The randomization sequence will be generated using R2.0 software. A designated researcher will prepare the assignments in opaque envelopes in sequence. The acupuncturists will only know of the group assignment prior to the treatment.

This trial is financed by the National Basic Research Program (No. 2011CB505203). The research protocol has been approved by the Clinical Trial Ethics Committee of Tongji Medical College, Huazhong University of Science and Technology (approval no. FWA00007304) and registered on the ClinicalTrials.gov protocol registration system (
http://clinicaltrials.gov/ct2/show/NCT01781897, ClinicalTrials.gov ID: NCT01781897).The duration of this study is 9 weeks for each patient: a screening period of 1 week, a treatment period of 4 weeks, and a follow-up period of 4 weeks. Constipation diaries are required to record at least 1 week before randomization as baseline data and this course will be continue to 8 weeks if they are eligible for this trial. All outcomes are assessed at baseline and 2, 4, and 8 weeks after randomization according to the diaries. A total of 16 sessions of acupuncture treatment will performed over a period of 4 weeks and each session will last 30 min after randomization. Five times a week in the first 2 weeks and three times a week in the last 2 weeks (Figure 
1).

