### Statistical analysis

Statistical analysis of all data will be done by the Department of Epidemiology and Biostatistics, School of Public Health, Tongji Medical College, Huazhong University of Science and Technology, which is blinded to this trial. SPSS 17.0 software packages will be used to analyze the data. All data are provided as mean ± standard deviation (SD) in continuous data and as frequency/percentage in categorical data. All of the analyses will be based on both an intention-to-treat analysis (ITT) and a treated-per-protocol analysis (TPP). The intention-to-treat (ITT) population was defined as the patients who are randomized and received at least one treatment session. The missing data will be dealt with the last observation value carried forward (LOCF) method. The per-protocol (PP) population was defined as the patients who have no major protocol violations in the ITT set. Both results of analysis will be compared to check whether the results are consistent.

Comparisons among baseline characteristics in different groups will be analyzed at first by analysis of variance, Chi-square test, and others. Then analysis will be applied to compare the effects of intervention between groups. Chi-square test will be used for comparison of categorical variables and analysis of variance of repeated measures will be performed for continuous parameters between the groups. The level of significance was set a P value less than 0.05.

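### The sample size does not follow from its own inputs: 90% power needs 75 per group rather than 71, and 81 per group does not leave 71 after 15% loss

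*Protocol article*

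**What the plan says.** All the figures stand in the protocol article, under Sample size calculation.

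- Drug arm: the defecation rate "was 2.6 times per week with a standard deviation of 2.2 after drug treatment", taken from a cited study.
- Acupuncture arm: "an improvement of the mean defecating frequency is 4.0 after acupuncture treatment, with a standard deviation of 3".
- Relevance: "a 1.4-fold difference in the clinical effects between the drug and the placebo is considered to be of clinical relevance".
- Result: "we need a sample size of 71 in each group", at alpha 0.05 and beta 0.10.
- Loss: "To allow 15% for loss to follow up, our proposed trial requires 243 patients (81 for each group").

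The section names neither the formula nor the sidedness and gives only a reference for the calculation. The Statistical analysis section adds: "The level of significance was set a P value less than 0.05". The Design section gives equal allocation to the three arms.

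**The concern.** Every input needed for a two-group comparison of means is printed, and so are both results, so the calculation can be checked directly. The 71 is smaller than the usual formula returns. The step from 71 to 81 looks like multiplication by 1.15 where division by 0.85 was needed.

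Both discrepancies make the design look stronger than it is. At stake are the stated 90% power and the statement that 243 patients absorb a 15% loss. The calculation is also the most favourable case: one pair of arms at one time point, with no allowance for multiplicity.

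**Working it through.** **Inputs (Sample size calculation):** means 2.6 and 4.0, so the difference is 1.4; SDs 2.2 and 3; alpha 0.05; power 0.90; loss 15%. Two assumptions are needed. The test is taken as two-sided, and 4.0 is read as the mean weekly frequency after acupuncture, comparable with the 2.6.

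**Step 1: the number per group before loss**

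n = (z₀.₉₇₅ + z₀.₉₀)² × (SD₁² + SD₂²) / difference²

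= (1.960 + 1.2816)² × (2.2² + 3²) / 1.4²

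= 10.507 × 13.84 / 1.96 = 74.2, so **75 per group**. With the t distribution it is 76.

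**Step 2: other routes to 71**

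| Variant (difference 1.4, 90% power unless noted) | n per group |
|---|---|
| One-sided, stated SDs | 61 |
| Common SD 2.2, two-sided | 52 |
| Common SD 2.6 (simple average of the two SDs), two-sided | 73 |
| Common SD 3, two-sided | 97 |
| Bonferroni over two or three comparisons, stated SDs | 88 or 96 |
| Three-group ANOVA, third mean 2.6, SD 2.63 throughout | 69 |
| Three-group ANOVA, third mean 2.6, SDs 3/2.2/2.2 | 62 |
| Difference 1.04, SD 2.2 in both arms, **80%** power | 71 |

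SD 2.63 is √(13.84/2). The last row does return 71. It reads the 1.4-fold criterion as a ratio (2.6 × 1.4 = 3.64, and 3.64 − 2.6 = 1.04), but it contradicts the stated mean of 4.0, SD of 3 and beta of 0.10.

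**Step 3: the allowance for loss.** This step needs no assumption about the test.

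- 71 × 1.15 = 81.65, which cut down to a whole number is the printed 81.
- Left after 15% loss: 81 × 0.85 = 68.85, about 69 and below 71.
- Needed to keep 71: 71 / 0.85 = 83.5, so 84 per group, 252 in total.
- Largest loss at which 81 still leaves 71: 1 − 71/81 = 12.3%.

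**Step 4: both corrections together**

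75 / 0.85 = 88.2, so 89 per group and 3 × 89 = 267 in total. The planned 243 is 24 fewer (24/267 = 9%).

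**Step 5: power actually delivered**

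Power ≈ Φ(1.4 / √(13.84/n) − 1.960)

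| n analysed per group | Normal | t-based |
|---|---|---|
| 71 | Φ(3.171 − 1.960) = 88.7% | 88.2% |
| 69 | Φ(3.126 − 1.960) = 87.8% | 87.3% |
| 81 (no loss) | Φ(3.387 − 1.960) = 92.3% | 92.0% |

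**The case against.** The best defence has three parts.

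**The method is not stated.** The trial has three arms and plans a repeated-measures analysis of variance, so the authors may have used a three-group calculation. With SD 2.63 throughout, a one-way ANOVA needs 69 per group if the mosapride-plus-sham mean is 2.6 and 73 if it is 2.7, so 71 lies within reach. That is true, but it requires a third mean that the article never gives. The text sets out one pair of means and sizes the trial to detect the difference between them. The fair statement is that no standard calculation on the printed inputs alone gives 71; how the authors reached it is unknown. The 71 × 1.15 route to 81 is likewise an inference.

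**Intention-to-treat with last observation carried forward keeps lost patients in the analysis.** With all 81 analysed, nominal power is about 92%. But carried-forward values do not restore the information assumed for completers, a per-protocol analysis is also planned, and the sample size section itself budgets for 15% loss. Having made that allowance, the article must compute it correctly.

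**The gap is small.** This stands. The difference detectable with 90% power at 71 per group is √(10.507 × 13.84/71) = 1.43 rather than 1.40 per week, and the uncertainty in the anticipated SDs is far larger than four patients. It bears on how serious the error is, not on whether the figures are wrong.

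**Conclusion.** The concern holds. The loss allowance is wrong whatever test is assumed: 81 per group leaves about 69 after 15% loss, not 71. The 71 is not reproduced from the stated means, SDs, alpha and beta. The two-sided two-sample calculation gives 75 (76 by t), and a one-sided reading, at 61, does not explain the figure either.

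Both errors overstate power. On the article's own inputs, power for electro-acupuncture versus mosapride with about 69 evaluable per group is about 87–88%, so beta is about 0.12 to 0.13 instead of 0.10. That is a shortfall of two to three percentage points. It is a misstated design figure and does not make the trial seriously underpowered. The conclusion assumes a two-sided test and a pairwise comparison at one time point, with no adjustment for multiplicity.

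**What to change.** Keep 243 and correct the statement. Suggested wording: *With 81 patients per group and 15% loss (about 69 evaluable per group), the comparison of electro-acupuncture with mosapride has about 87–88% power to detect mean weekly defecation frequencies of 4.0 versus 2.6 (SD 3 and 2.2) at a two-sided significance level of 0.05.*

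With it:

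- Remove the 71, and compute the loss allowance as n/(1 − 0.15).
- Name the formula and the sidedness, and say that the figure covers this pair of arms only.
- Reconcile the 1.4-fold criterion with the absolute difference of 1.4, since a ratio of 1.4 on 2.6 is a difference of 1.04.

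The cost is a sentence or two and a slightly less favourable power figure. No further patients are needed. If 90% power after 15% loss must be kept, the price is 89 per group, 267 in total.

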### Statistical analysis

Statistical analysis of all data will be done by the Department of Epidemiology and Biostatistics, School of Public Health, Tongji Medical College, Huazhong University of Science and Technology, which is blinded to this trial. SPSS 17.0 software packages will be used to analyze the data. All data are provided as mean ± standard deviation (SD) in continuous data and as frequency/percentage in categorical data. All of the analyses will be based on both an intention-to-treat analysis (ITT) and a treated-per-protocol analysis (TPP). The intention-to-treat (ITT) population was defined as the patients who are randomized and received at least one treatment session. The missing data will be dealt with the last observation value carried forward (LOCF) method. The per-protocol (PP) population was defined as the patients who have no major protocol violations in the ITT set. Both results of analysis will be compared to check whether the results are consistent.

Comparisons among baseline characteristics in different groups will be analyzed at first by analysis of variance, Chi-square test, and others. Then analysis will be applied to compare the effects of intervention between groups. Chi-square test will be used for comparison of categorical variables and analysis of variance of repeated measures will be performed for continuous parameters between the groups. The level of significance was set a P value less than 0.05.

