**Methods:**

The current trial is a multicenter, randomized, three-arm controlled study undergoing in China. About 243 people who aged from 18 to 65 years with FC will be recruited in this study. These participants will be randomly allocated into three treatment groups, including electro-acupuncture (EA), Mosapride (M) and Mosapride & Sham Electro-acupuncture (MS) groups in a 1:1:1 ratio. Both the EA and sham EA receives 16 sessions of needling at Quchi (LI11) and Shangjuxu (ST37) during 4 weeks of treatment, and a follow-up period of 4 weeks. These groups will be compared on the primary outcomes of the number of times of defecation at baseline and 2, 4, 8 weeks after randomization. The secondary outcome measures include: stool consistency, intensity of defecating difficulty, MOS item Short Form health survey (SF-36), Self-Rating Anxiety Scale (SAS), Self-rating Depression Scale (SDS), and the validated Patient Assessment of Constipation Quality of Life (PAC-QOL). These outcomes are measured at baseline and 2, 4 weeks after randomization, but SF-36 is measured at baseline and 4 weeks after randomization.

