### Mosapride (M) group

Participants assigned to this group will receive 5 mg Mosapride Citrate tablet (Dainippon Sumitomo pharmaceutical Co.Ltd, Japan) three times a day for 4 weeks continuously, in the form of an oral capsule administered at least 30 minutes before eating.

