Acupoints selected in this trial were Quchi (LI11) and Shangjuxu (ST37), which were He-Sea and Lower He-Sea points of Large Intestine meridians. According to traditional acupuncture theories, both of them have a positive therapeutic effect in treating internal organ disease. Differing from the other studies adopted non-acupoints in placebo control, we will use a validated placebo needling
[9] and special electrode lines with no current output at the same acupoints to mimic as closely as possible the real situation on patients. In the other hand, to avoid communication with each other, patients will be assigned to acupuncture treatments alone at different times. In addition, we will use mosapride as a positive control group because it has been confirmed as an effective drug to treat FC in China and western countries. The primary outcome assessment will be collected from the diaries which will be convenient and easy for patients to record. Certainly, the safety of interventions is needed to consider during the whole process.

As far as we know, this is the first acupuncture trial adopting sham EA combined with mosapride (MS) as a control to observe the efficacy of acupuncture for treating FC. The reasons we selected mosapride & sham acupuncture as a control instead of simple placebo acupuncture based on: Firstly, it will help to improve therapy compliance and reduce the rate of drop-out so as to ensure that the study is completed smoothly, because a big part of patients expect to receive acupuncture treatment when they participate in this trial. Second, whether simple placebo acupuncture is effective for patients with functional constipation is controversial, so it accords with the ethical principles of beneficence and justice to avoid ethical confusion.

However, some limitations we must also recognize that patients are not blinded in this trial. The participants will know whether they receive acupuncture or medication although they will not know true or sham acupuncture they will receive. And then, the physiological effects may be amplified when patients have a higher positive beliefs and expectations of benefit of acupuncture compared with medicine, which will impact the acupuncture effect. These factors will lead to a bias of the outcome assessment. In conclusion, the study will supply significant evidence for using acupuncture to treat FC, and help us to observe whether it is a therapeutic effect rather than a placebo effect.

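### The set labelled intention-to-treat admits only patients who had a treatment session; the criterion is undefined for the tablet-only arm, and no planned analysis covers all randomised patients

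*Protocol article*

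**What the plan says.** The Statistical analysis section gives two analysis sets and runs every analysis on both. The first is defined thus: "The intention-to-treat (ITT) population was defined as the patients who are randomized and received at least one treatment session". The second is nested in it: "The per-protocol (PP) population was defined as the patients who have no major protocol violations in the ITT set". On how the two relate, the section says only: "Both results of analysis will be compared to check whether the results are consistent". Missing values are handled by one rule: "The missing data will be dealt with the last observation value carried forward (LOCF) method".

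The Abstract (Methods) ties sessions to needling: "Both the EA and sham EA receives 16 sessions of needling at Quchi (LI11) and Shangjuxu (ST37) during 4 weeks of treatment". The Design section, the EA group section and Table 1 use the word in the same way. The M arm receives mosapride tablets "three times a day for 4 weeks continuously", and no session is described for it. The combined arm (MS) receives both the tablets and the sham sessions.

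The Discussions section acknowledges that patients are not blinded to acupuncture versus medication; only true versus sham needling is masked. In explaining why sham needling was added to mosapride in MS, it says that "a big part of patients expect to receive acupuncture treatment when they participate in this trial", and links this to compliance and drop-out.

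**The concern.** An intention-to-treat set keeps the groups as randomisation formed them. Requiring a treatment session makes entry depend on something that happens after allocation. That is usually harmless when allocation cannot influence whether treatment starts. Here patients know whether they got needles or tablets, and the article itself ties the wish for acupuncture to drop-out. M is the only arm without needling.

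If some patients leave on learning that they will get tablets only, the rule removes them from M with no matching removal from EA. The article also warns that belief in acupuncture may amplify its effects, so those who leave may differ in outcome from those who stay. At stake is the contrast of acupuncture with drug treatment, which is the one behind the sample size. The label ITT would tell readers that the randomised comparison had been preserved when the rule does not ensure it.

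**Working it through.** **1. Apply the entry rule to each arm.**

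| Arm | Treatment described | Does 'at least one session' have a meaning? |
|---|---|---|
| EA | 16 needling sessions | Yes |
| MS | 16 sham sessions plus tablets | Yes, but a patient who took tablets and attended no session is left unclear |
| M | Tablets three times a day | Not defined |

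The rule is therefore not the same test in the three arms.

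**2. Look for a set that covers everyone.** Per-protocol lies inside the 'ITT' set, and the 'ITT' set lies inside all randomised patients. Only the first two are analysed, so a patient randomised but never treated appears in no planned analysis.

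**3. Ask whether allocation can influence entry.** Patients know acupuncture from medication, and many expect acupuncture (Discussions). Influence is possible. No rate of exit before first treatment is given anywhere.

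**4. Illustrate the size under assumptions.** The plan has no figure of its own to reproduce on this point. From Sample size calculation: means 4.0 and 2.6 (difference 1.4), SDs 3 and 2.2, 71 per group before drop-out and 81 after.

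- Planning standard error: sqrt((2.2² + 3²)/71) = sqrt(13.84/71) = 0.44 per week.
- In one arm, let a fraction p be excluded, and let stayers exceed leavers by d per week. The treated-only mean then exceeds the all-randomised mean by p × d. With the same d in both arms, the EA minus M contrast moves by (p_EA − p_M) × d.
- Assume p_M = 0.15 (0.15 × 81 ≈ 12 patients), p_EA = 0.02 (0.02 × 81 ≈ 2 patients) and d = 1. The shift is (0.02 − 0.15) × 1 = −0.13 per week. In absolute size that is 0.13/1.4 = 9% of the planned difference and 0.13/0.44 = 0.30 of a standard error.
- For an excess loss in M of 5% to 15% and a gap of 1 to 2 per week, the absolute shift runs from 0.05 × 1 = 0.05 to 0.15 × 2 = 0.30 per week, or about 4% to 21% of 1.4.
- The sign follows d. If leavers would have done worse than stayers, dropping them flatters M; if better, it flatters EA. The documents do not say which.

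**5. Check what LOCF does once everyone is included.** A patient who leaves untreated and returns no later diary is represented by the baseline value, that is, by no change. If the excess 13% in M were handled this way and would in truth have improved by 1 per week, the M mean would be too low by 0.13 × 1 = 0.13 per week, in favour of EA. Widening the set without collecting later diaries could therefore replace one distortion with another of similar size.

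**The case against.** Several objections carry weight.

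- **Literal exclusion of M.** A reader might infer that the whole M arm, 81 of 243 patients (33%), falls outside the set. The documents do not support this as a real prospect. The trial is a three-arm comparison throughout, the phrase is treatment session rather than acupuncture session, and no analyst would discard a randomised arm. The authors probably meant any treatment. What stands is that they do not say so, and no common start-of-treatment rule is given.
- **Two chances of success.** A reader might infer that running both sets gives two routes to a positive result. The text describes a check of consistency, not an either-or success rule. Ranking of the sets may also be fixed in an analysis plan that is not shown. Nor does the article call the ITT analysis the main one. This does not rescue the plan, because both sets carry the same restriction.
- **Refusals concentrating in M.** This is an inference. The remark about expecting acupuncture explains the design of MS and does not forecast exits before treatment. Table 1 puts consent and randomisation in the same week, and the Inclusion criteria require patients to volunteer for the whole study, so the window for early exit may be short. Differential exit remains plausible, but it is not shown.
- **Size.** Every exit rate used above is assumed. The 15% for M equals the trial's entire allowance for loss to follow-up, all placed before the first tablet. Even so, the shift of 0.13 is under a third of the planning standard error.

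**Conclusion.** The concern holds as a fault in a stated definition. The set called intention-to-treat is a treated-only set, its entry criterion is undefined for M, and the nesting of per-protocol within it leaves no analysis of all randomised patients. Because allocation to needles or tablets is known, entry could depend on allocation and bias EA versus M.

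The size and direction of that bias cannot be computed from the documents. The illustrative 0.05 to 0.30 per week rests wholly on assumed exit rates and an assumed gap between leavers and stayers, and shows only the order of magnitude. If few or no patients leave before first treatment, the effect is negligible. The case for changing the definition is that the risk is avoidable at little cost, not that a distorted result has been demonstrated.

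**What to change.** - Define the ITT set as all randomised patients, analysed in their allocated arm whatever treatment they received. Use it for the primary outcome, with per-protocol as supportive.
- Keep requesting diaries from patients who decline or stop treatment, through the scheduled assessments. The change depends on this: otherwise untreated leavers enter only as a baseline value carried forward.
- If a treated-only set is kept, call it modified ITT and give it a start criterion that applies in all three arms, for example first needling session or first study tablet.
- Report by arm how many patients were randomised but never started treatment.

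The cost is a change of wording, some extra diary follow-up, and possibly a slightly diluted estimate. As an illustration, suppose k of 81 EA patients go untreated and have the drug-arm mean of 2.6. A treated-only difference of 1.4 then becomes 1.4 × (1 − k/81): 1.38 for k = 1, 1.33 for k = 4, 1.26 for k = 8 and 1.19 for k = 12. The Trial status section says recruitment was still under way, so on the article's account the diary requests could still be put in place.

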### Outcome measures

The primary outcomes of the study is the times of defecation per week at baseline and at the 2nd, 4th and 8th week after randomization. Secondary efficacy end points include: 1) stool consistency
[10]; 2) intensity of defecating difficulty; 3) MOS item Short Form health survey (SF-36)
[11]; 4) Self-Rating Anxiety Scale (SAS)
[12]; 5) Self-rating Depression Scale (SDS)
[13]; 6) the validated Patient Assessment of Constipation Quality of Life (PAC-QOL)
[14] (Table 
1).

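### LOCF is the only missing-data method named, so on-treatment counts can be entered as the off-treatment week-8 result, with bias in either direction

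*Protocol article*

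**What the plan says.** In the protocol article, Outcome measures defines the primary outcome as "times of defecation per week at baseline and at the 2nd, 4th and 8th week after randomization". Design gives each patient "a treatment period of 4 weeks, and a follow-up period of 4 weeks", and the Mosapride (M) group section gives the drug "three times a day for 4 weeks continuously". Week 8 is thus a primary time point four weeks after all treatment has ended.

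Statistical analysis says "The missing data will be dealt with the last observation value carried forward (LOCF) method" and that "analysis of variance of repeated measures will be performed for continuous parameters between the groups". Its intention-to-treat set is "patients who are randomized and received at least one treatment session", so one session is enough to be included. The only robustness check is to compare the intention-to-treat and per-protocol results. Sample size calculation adds patients with the words "To allow 15% for loss to follow up", but nothing says how that loss would divide between arms or over time.

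**The concern.** LOCF assumes that a patient's count stays where it was last seen. Here that assumption has to hold across the end of treatment. For anyone lost between weeks 4 and 8, persistence of the effect is assumed at the one visit where it should be measured. At the other end, a patient treated once and lost before the week-2 assessment has only a baseline value to carry, and keeps it through weeks 2, 4 and 8.

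The filled-in values then enter the repeated-measures ANOVA as if observed, which overstates the information available. The intention-to-treat versus per-protocol comparison changes which patients are analysed and does not test the carry-forward assumption.

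What is at stake is the between-group estimate on the primary outcome, most directly at week 8.

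**Working it through.** **Inputs from Sample size calculation.** Drug mean 2.6 (SD 2.2). Acupuncture 4.0 (SD 3), read as a post-treatment level like the drug figure. Difference 1.4, α = 0.05 (taken as two-sided), power 90%, 71 per group before loss, 15% loss, 81 per group.

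**The plan's own figure.** With the averaged SD of 2.6, the standard two-means formula gives 73 per group. With the root-mean-square SD, √((2.2² + 3²)/2) = 2.63, it gives 75, and power at 71 is 88.7%. The stated 71 is therefore reproduced closely, and 2.63 is a reasonable SD for the checks below.

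**Standard error.** At 81 per arm, SE = 2.63 × √(2/81) = 0.413. For a bias b with no true difference, the rejection probability is P(|Z + b/SE| > 1.96). The SE is left unchanged, so any understatement of variance by LOCF is not included and is not quantified here.

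**Check 1: loss after week 4.** Assume the same loss in both arms, a 1.4 difference at week 4 and none at week 8. Bias = share lost × 1.4.
- 15% lost: 0.15 × 1.4 = 0.21 per week; b/SE = 0.51; type I error about 8.0%.
- 5% lost: 0.07 per week; 5.3%.
- 30% lost: 0.42 per week; 17.4%.
- Half the late loss (0.075 × 1.4) or half the fade (0.15 × 0.7): 0.105 per week; b/SE = 0.25; about 5.7%.

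These error rates are for a stand-alone week-8 comparison.

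**Check 2: unequal loss before week 2.** Assume the arms are truly equal. Bias in favour of electro-acupuncture (EA) = (loss in M − loss in EA) × (true mean − baseline). The article gives no baseline mean and no drop-out by arm, so these are assumptions.
- 25% in M and 5% in EA, baseline 1.9, true mean 2.6 (the article's post-drug figure): 0.20 × 0.7 = 0.14 per week; about 6.3%.
- 15% in M and 5% in EA, baseline 1.0 to 2.0, true mean 2.6: 0.16 down to 0.06 per week; 6.7% down to 5.2%.
- Same split and baselines, true mean 4.0: 0.30 down to 0.20 per week; 11.2% down to 7.7%.
- 5% in M and 15% in EA, baseline 1.0 to 2.0, true mean 2.6: −0.16 to −0.06 per week. The sign reverses.

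**Check 3: equal loss before week 2 with a true effect.** Assume 15% in each arm and baseline 1.5.
- EA: 0.85 × 4.0 + 0.15 × 1.5 = 3.625.
- M: 0.85 × 2.6 + 0.15 × 1.5 = 2.435.
- Difference: 1.19 instead of 1.4, so a true effect shrinks.

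**The case against.** A reader might infer that LOCF systematically favours EA because the article itself predicts more drop-out on mosapride alone. The Discussions section does say that "a big part of patients expect to receive acupuncture treatment when they participate in this trial" and that the chosen control should reduce drop-out. But that argument explains why mosapride plus sham was preferred to placebo acupuncture alone. It makes no prediction for the M arm. Excess loss in M is plausible, because patients there receive no needling and know it. Excess loss in EA is plausible too, because that arm requires 16 visits, five a week at first. The documents fix neither direction.

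A reader might also arrive at larger figures. With 25% versus 5% early loss, baseline 1.9 and a common true mean of 3.5, the bias is 0.20 × 1.6 = 0.32 per week and the type I error about 12%. The baseline, the common mean and the loss split appear nowhere in the article.

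Three further points limit the size:
- Check 1 at 15% needs all the loss to fall after week 4 and the whole effect to vanish. It cannot apply at full size together with heavy early loss.
- The 8% is not the error rate of the planned repeated-measures ANOVA. With a real difference at week 4, the overall null hypothesis is already false.
- The article makes no explicit durability claim; week 8 is one of several primary time points.

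It can also be said that further sensitivity analyses may sit in an unseen analysis plan, and that reasons for drop-out will be recorded. Both points are fair, but the article positively names LOCF, and recording reasons does not correct the estimate. For a patient who stopped treatment very early, baseline may even be near the truth. That depends on the effect being estimated, which the article does not state.

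**Conclusion.** The point stands as a should-fix weakness. LOCF is the sole stated method, and it carries values across the end of treatment into a primary time point. At the planned 15% loss the week-8 artefact is at most about 0.21 per week when loss is equal across arms and the difference fades no further than zero. That is 15% of the 1.4 design difference, with a type I error of about 8% for a stand-alone week-8 test. It falls to about 0.105 per week and 5.7% if half the loss is late or half the effect fades.

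Bias from early loss rests on assumed baselines and drop-out splits. It is about 0.14 per week in the 25% versus 5% case with the article's post-drug mean, and it reverses if EA loses more patients. Equal early loss shrinks a true effect. The documents support neither a guaranteed false benefit for EA nor a claim that LOCF is safely conservative.

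**What to change.** Replace LOCF and repeated-measures ANOVA as the primary analysis with a likelihood-based mixed model for repeated measures on all observed weekly counts. Keep baseline in the model as a response alongside weeks 2, 4 and 8, so that patients lost before week 2 still contribute, and report the week-8 contrast from this model.

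Add one sensitivity analysis for data missing not at random, for example reference-based multiple imputation using the M-arm profile. Imputing each drop-out toward their own baseline is less useful here, because it partly repeats the assumption being questioned. Keep LOCF at most as a secondary sensitivity analysis.

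The cost is revised analysis wording and slightly more programming, with no new data. The downside is that the mixed model assumes data are missing at random. Patients lost before week 2 supply only a baseline value, so they add little direct information on the treatment contrast, which is why the sensitivity analysis is needed.
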